### Study Period

A participant’s involvement in the study will end after 4 to 6 weeks. The schedule of this study will include enrollment, allocation, weekly phone call, and closeout visit at the time of patient admission (Table 1). We will also collect information after patient discharge.

**Table 1 table1:** Study schedule for clinical study visits.

Time point		Study period				
		Visit 0	Visit 1	Follow-up	Closeout	Discharge
**Enrollment**						
	Selection criteria review	✓				
	Informed consent	✓	✓			
	ID number	✓				
	Randomization		✓			
**Intervention**						
	Arm A (placebo)		✓			
	Arm B (experimental)		✓			
	Compliance			✓	✓	
**Assessment**						
	Nutritional evaluation		✓		✓	
	Quality of life		✓		✓	
	Medical history		✓			✓
	Complication rate (Clavien-Dindo)					✓
	Adverse effects			✓	✓	
	Fecal and blood sample collection		✓		✓	

At visit 0, we will review inclusion and exclusion criteria. Patients who meet the criteria will be informed about the study and assigned an ID number. The principal investigator will record and keep this number appropriately. Patient will receive the informed consent and a device to collect a fecal sample at home.

At visit 1 (baseline), if patient agrees to participate in the study, we will perform randomization. We will also evaluate nutritional status and perform the quality of life assessment. Previous medical history will be recorded, fecal sample will be obtained from the patient, and blood samples will be collected. If malnutrition is detected, we will refer the patient to nutrition consultation. Additionally, the patient will receive another device to collect the needed fecal sample at the end of the study.

Follow-up visits will be performed weekly for 4 to 6 weeks. We will use this weekly phone call to collect data about adverse effects and treatment compliance.

Closeout visit will be done at the same time as patient admission. The intervention will end at this time, and patients will return the remaining treatment to researchers. We will also pick up fecal and blood samples, evaluate the nutritional status, and assess quality of life again. Further, data about adverse effects will be collected.

The end of the study will be defined by patient discharge. We will evaluate and classify the surgery complications at this time. Data collection will include information about antibiotic prophylaxis used, length of stay, vital status, surgery performed, and final staging of the CRC according to the TNM.

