#### Adverse Effects

Adverse events and their severity will be collected using the Common Terminology Criteria for Adverse Events (CTCAE) version 5.0 [41]. The principal investigator will be responsible for reporting adverse effects of interest and serious events to the sponsor. The sponsor must immediately report possible serious events that may be related to the treatment.

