## Discussion

### Principal Findings

The trial has been designed to evaluate the effects of a new dietary supplement on complications associated with surgery in CRC patients. The results, if positive, may provide a change in the current guidelines for preoperative care in CRC. Additionally, this study protocol will confirm the safety of the Micodigest 2.0 supplement and evaluate patient adherence to this new treatment. In sum, the results may provide a simple, safe, and inexpensive intervention with good adherence rates to reduce surgery complications and consequently improve the quality of life of CRC patients.

The protocol is necessary not only to study the effects of Micodigest 2.0 but also to investigate patterns and features related to complications after surgery. The results may show clinical features, inflammatory patterns, or nutritional statuses associated with postoperative complications. Moreover, the results could show new effects of gut microbiota on surgery complications. Therefore, the protocol could identify risk factors for postoperative complications and contribute to the design of new clinical studies to prevent CRC surgery complications.

Interest in the role of fungal polysaccharides in gut microbiota and immune regulation has increased in recent years. The results of this study may improve the knowledge about the biological functions of fungal polysaccharides. Further, this trial may help to define new health benefits of these bioactive polysaccharides and design new studies on their use in CRC patients. Hence, the use of fungal polysaccharides as probiotics could introduce a new step in the prevention and treatment of CRC. Bioactive polysaccharides may improve the response to treatment, especially immunotherapies, due to their immunomodulating activity. These polysaccharides could also increase the safety of treatments commonly used in cancer and alleviate adverse effects of these therapies. Additionally, the anti-inflammatory activity of fungal polysaccharides could influence carcinogenesis, progression, and tumor metastasis.

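### Scheduled adverse-event collection ends at admission, on the day dosing stops and before surgery, although the study runs to discharge and safety is a secondary objective

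*Protocol article*

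**What the plan says.** All references are to the protocol article.

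- **Dosing.** Under Intervention, both arms take the product or placebo until admission for surgery, a period of 4 to 6 weeks.
- **Adverse-event contacts.** Under Study Period, the weekly calls are the first source: "We will use this weekly phone call to collect data about adverse effects and treatment compliance". The second is closeout, where the text lists sampling, nutrition and quality of life and then adds: "Further, data about adverse effects will be collected". Closeout coincides with admission: "Closeout visit will be done at the same time as patient admission. The intervention will end at this time". Table 1 agrees, with ticks under Follow-up and Closeout and none under Discharge.
- **End of study.** "The end of the study will be defined by patient discharge". At that point the text says: "We will evaluate and classify the surgery complications at this time". The other discharge items are antibiotic prophylaxis, length of stay, vital status, surgery performed and final stage. Under Medical History, the discharge data include type of complication and Clavien-Dindo category.
- **Grading and reporting.** The Adverse Effects section specifies CTCAE version 5.0 and says: "The principal investigator will be responsible for reporting adverse effects of interest and serious events to the sponsor". It gives no start or end of the window.
- **Use of the data.** Safety is the first secondary objective listed in the Introduction. Inferential Statistics plans two separate comparisons between arms, one of complications and one of reported adverse events, each with chi-square tests and a risk ratio with 95% confidence interval. The Discussion states that "this study protocol will confirm the safety of the Micodigest 2.0 supplement".

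**The concern.** Patients go directly from the last dose to colorectal surgery. The stretch from admission to discharge is the only time after exposure in which the trial still observes them, and the schedule places no adverse-event assessment there. The adverse-event comparison would then describe the weeks at home before surgery. An in-hospital event that nobody classes as a surgical complication would have no scheduled route into either comparison. An event that is so classed would appear in the complication analysis, but without a scheduled CTCAE grade and outside the adverse-event table. A conclusion that the product is safe in these patients would then rest on two records with different scales and different periods, and the article does not say how they combine.

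**Working it through.** No plan figure is at issue, so the check sets the stated schedule against the stated uses of the data.

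1. **Length of the scheduled window.** Start: first dose, after randomisation at Visit 1. End: closeout. With 4 to 6 weeks of dosing this is 4 × 7 = 28 to 6 × 7 = 42 days.
2. **Follow-up after the last dose.** Closeout is at admission and dosing ends at admission. Last scheduled collection minus end of dosing = 0 days.
3. **Position relative to surgery.** Admission precedes the operation, so the window closes before any operative exposure. Table 1 and the visit text agree, so an isolated slip in the table does not explain it.
4. **What is recorded for each period.**

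| Period | Scheduled adverse-event (CTCAE) collection | Other harm data | Comparison between arms |
|---|---|---|---|
| First dose to admission | Weekly calls and closeout | None listed | Adverse events |
| Admission to discharge | None | Complication type, Clavien-Dindo category, vital status | Complications |

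5. **What falls between the two.** Two groups remain. In-hospital events not classed as surgical complications have no scheduled collection. In-hospital events that are so classed are recorded, but outside the CTCAE data. The list of discharge items also contains no entry for relatedness to the product, whereas the Adverse Effects section ties the sponsor's onward reporting to a possible relation to treatment.
6. **How large the first group is.** This depends on how broadly a surgical complication is defined. The Introduction's list of common complications is broad and includes infection, ileus, thrombosis, and pulmonary and cardiac events. Read broadly, few events would be left over. Read narrowly, more would. The documents give no rate for such events, so no count can be derived.
7. **Statements about the end of participation.** Study Period opens by saying that a participant's "involvement in the study will end after 4 to 6 weeks". The visit description says "The end of the study will be defined by patient discharge". The opening paragraph also says that information will be collected after discharge. The three can be reconciled if the 4 to 6 weeks mean active treatment, but the text does not say so.

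**The case against.** The strongest reply is that in-hospital harm is what this trial measures best. Complications are the main end point, are classified by type and by the 5 Clavien-Dindo categories, and are compared between arms by severity and type. Deaths up to discharge are covered by vital status. Keeping end-point events out of the adverse-event table also avoids counting the same event as both efficacy and safety. All of this stands, and it limits the point.

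Three stronger readings are tempting, and the documents do not support them.

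- A reader might infer that the trial omits operative harm altogether. It does not, because complications and vital status are collected at discharge.
- A reader might take the expected number of patients with complications, 72 × 0.40 + 72 × 0.20 = 43.2 of 144 on the Sample Size assumptions, as the amount of safety data lost. Those patients are captured and analysed in the primary comparison. The figure measures morbidity after the adverse-event window, not missing data.
- A reader might infer that serious events after admission would go unreported. The Adverse Effects section sets no end date for the investigator's duty, and the assessment schedule does not limit it. What can be said is that the window is unstated and that no scheduled adverse-event collection feeds it after closeout.

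It can also be said that an article leaves reporting windows and relatedness procedures to the full protocol. That is fair for those details. It does not answer the point about the schedule, because the article prints a visit table and a list of discharge data, and both leave adverse events out at discharge.

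**Conclusion.** The point holds in a limited form. As scheduled, CTCAE adverse-event collection covers first dose to admission only, with 0 days after the last dose and none of the hospital stay. After admission, harm is captured only as Clavien-Dindo complications and vital status. The adverse-event comparison therefore cannot by itself support a safety conclusion that includes the operative period, and in-hospital events outside the complication record have no scheduled collection.

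The primary end point and its analysis are unaffected. The number of events at stake cannot be estimated from the documents. The conclusion assumes that Table 1 and the visit text describe what will actually be collected. A full protocol that schedules adverse events through discharge would settle the matter, and the article would then need correcting. The wording on when participation ends is loose rather than a firm contradiction, but should be aligned. This should be amended, because safety is a stated objective and the change is small.

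**What to change.** 1. In Table 1, tick the adverse-effects row under Discharge, and add adverse events to the discharge data listed in the visit description.
2. In the Adverse Effects section, state that CTCAE collection and serious-event reporting run from first dose to discharge.
3. In Inferential Statistics, report adverse events by arm separately for first dose to admission and for admission to discharge. Cross-refer to the complication record so that end-point complications are identified and not counted twice.
4. If collection is not extended, limit the safety statement in the Discussion to the period before admission plus recorded complications.
5. Align the opening of Study Period with the visit description, so that active treatment (4 to 6 weeks) and end of participation (discharge) are distinguished.

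**Cost.** Changes to protocol and case-report-form wording. The discharge contact and the complication record already exist, so no extra visit is needed. The downsides are slight overlap with the complication record, which the cross-reference handles, and a possibly less favourable adverse-event table.

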### Outcomes and Data Collection

#### Medical History

Data regarding inclusion and exclusion criteria, demographic variables, tumor location, tumor stage, and type and duration of symptoms will be collected at first visit. At the time of patient discharge, we will also recover data about type of surgery, length of stay, vital status, type of surgery complications, and stratification of postoperative complications according to the 5 categories in the Clavien-Dindo classification.

#### Nutritional Evaluation

We will use 4 anthropometric measures to evaluate nutritional status: weight, height, BMI, and body fat percentage. Nutritional status assessment will be based on the PG-SGA survey and albumin, prealbumin, total lymphocytes, and hemoglobin levels.

#### Quality of Life

We will use the 36-item Short Form Health Survey to evaluate the quality of life. This survey has been validated and is frequently used to assess quality of life in CRC patients [40].

#### Treatment Compliance

A staff study member will deliver treatment for 6 weeks at the baseline visit. The researchers will ask about compliance and quantity of treatment used at follow-up visits. Patient will return the remaining treatment at closeout visit. This delivery option has been proposed to minimize visits to the hospital and promote retention and completion of follow-up.

#### Adverse Effects

Adverse events and their severity will be collected using the Common Terminology Criteria for Adverse Events (CTCAE) version 5.0 [41]. The principal investigator will be responsible for reporting adverse effects of interest and serious events to the sponsor. The sponsor must immediately report possible serious events that may be related to the treatment.

#### Blood Samples

Blood samples will be collected at baseline and closeout visits. These samples will be stored at –20 ℃ until analysis. Laboratory analysis will include hemoglobin, mean corpuscular volume, mean corpuscular hemoglobin, albumin, prealbumin, C-reactive protein, creatinine, prothrombin time, neutrophil-lymphocyte ratio, IL-6, IL-10, and TNF-α levels.

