#### Inferential Statistics

We will apply inferential statistics to identify differences between the control and experimental groups. In general, dichotomous variables will be compared with chi-square tests, whereas qualitative variables with more than 2 categories will be compared with analysis of variance tests. Continuous variables will be compared with *t* tests for independent samples or Mann-Whitney *U* tests if they do not meet normality. *P*<.05 will be considered statistically significant. More specifically, to analyze the outcomes of the study the following statistical methodology will be performed:

We will analyze the complication rate after surgery in the 2 intervention groups. We will base this analysis on severity and type of complication. After stratification by tumor location, we will use chi-square tests to identify significant differences between the 2 groups. Risk ratio and 95% confidence interval will be used to describe the differences found.We will describe adverse events reported in each group. To find significant differences between the 2 groups, chi-square tests will be used after stratification by tumor location. Risk ratio and 95% confidence interval will be used to describe the differences found.Diversity and composition of the gut microbiota will be analyzed in the 2 groups using McNemar tests and *t* tests to identify significant differences between the groups.Inflammatory differences between the 2 intervention groups will be analyzed with *t* tests if variables meet normality or Wilcoxon tests if variables do not meet normality. We will also analyze the dynamic changes of the neutrophil-lymphocyte ratio in the 2 intervention groups.Differences in dietary pattern and quality of life will be analyzed with McNemar tests for qualitative variables and *t* tests for quantitative data.We will perform a univariate analysis to identify any associations between impact of the microbiome, inflammatory and dietary patterns, and surgery complications. We will perform a multivariate regression with the significant variables found. In addition, the model fit will be assessed using a likelihood-ratio test, area under the receiver operating characteristic curve, Akaike information criterion, and Bayesian information criterion, and we will then validate the model designed using the bootstrap method.

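### Blood Samples section: one freezing rule covers a panel that includes cell-based tests, so MCV, MCH and the neutrophil-lymphocyte ratio cannot be measured validly if it is followed as written

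*Protocol article*

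**What the plan says.** The Blood Samples section of the protocol article consists of three consecutive statements.

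- Timing: "Blood samples will be collected at baseline and closeout visits".
- Storage: "These samples will be stored at –20 ℃ until analysis".
- Panel, running straight on from the storage rule: "until analysis. Laboratory analysis will include hemoglobin, mean corpuscular volume, mean corpuscular hemoglobin", followed by albumin, prealbumin, C-reactive protein and creatinine, and ending with "prothrombin time, neutrophil-lymphocyte ratio, IL-6, IL-10, and TNF-α levels".

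The section does not separate whole blood from serum or plasma, and it exempts no test from the storage step. The Fecal Samples section then repeats the –20 ℃ rule for stool.

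Two other sections depend on cell counts from this blood. Nutritional Evaluation bases the assessment partly on "PG-SGA survey and albumin, prealbumin, total lymphocytes, and hemoglobin levels". Inferential Statistics, after the general comparison of inflammatory markers, adds a separate analysis: "We will also analyze the dynamic changes of the neutrophil-lymphocyte ratio in the 2 intervention groups".

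**The concern.** The storage sentence and the panel sentence cannot both be followed. Some of the listed tests need intact blood cells, and no sample kept at –20 ℃ and then thawed will supply them.

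The neutrophil-lymphocyte ratio matters most here, because it is the only inflammatory marker given its own analysis of change over time. Total lymphocytes are one of the four laboratory markers of nutritional status. Inflammatory pattern and nutrition status are both named in the secondary objectives. They may also enter the regression model for complications and the causal mediation analysis, but only if they pass the earlier selection steps.

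A count that was not made on fresh blood cannot be recovered later from the freezer. The loss would be permanent for each patient handled in this way.

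**Working it through.** No figure in the plan needs to be reproduced, and the point does not depend on sample size or power. The check is a count of the panel and a comparison of the sections.

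**Step 1. Count the panel.** The Blood Samples section lists hemoglobin, MCV, MCH, albumin, prealbumin, C-reactive protein, creatinine, prothrombin time, neutrophil-lymphocyte ratio, IL-6, IL-10 and TNF-α. That is 12 analytes. Total lymphocytes are not in this list; they appear only under Nutritional Evaluation.

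**Step 2. State what each cell-based test needs.**

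- MCV is the mean volume of intact red cells.
- MCH = hemoglobin ÷ red-cell count, so it needs a red-cell count even where hemoglobin itself can be read.
- Neutrophil-lymphocyte ratio = neutrophil count ÷ lymphocyte count, so it needs a differential on intact white cells.
- Total lymphocytes need the same differential.

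**Step 3. Apply the storage rule.** The text does not say which material is frozen, so both possibilities are taken.

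| Test | Whole blood frozen and thawed (cells lysed) | Only serum or plasma frozen (no cells) |
|---|---|---|
| MCV | not valid | not valid |
| MCH | not valid | not valid |
| Neutrophil-lymphocyte ratio | not valid | not valid |
| Total lymphocytes (Nutritional Evaluation) | not valid | not valid |
| Hemoglobin | concentration still readable | lost |
| Prothrombin time | at risk | at risk |

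The other seven listed analytes (albumin, prealbumin, C-reactive protein, creatinine, IL-6, IL-10 and TNF-α) are compatible with freezing once serum or plasma has been separated.

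**Step 4. Size.** MCV, MCH and the ratio fail under either possibility: 3 of 12 listed analytes, 3 ÷ 12 = 25%. Hemoglobin makes it 4 of 12 if only serum or plasma is kept. Prothrombin time is not added to the certain losses, because the article does not give the plasma handling or the storage time that would settle it. Outside the list, total lymphocytes are lost under both possibilities: 1 of the 4 laboratory markers under Nutritional Evaluation, or 2 of 4 if hemoglobin goes too.

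**Step 5. Reach.** Blood is drawn at 2 visits in 144 planned patients, so at most 2 × 144 = 288 samples fall under the rule.

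**Step 6. Look for an exception.** No section of the article provides for a same-day or fresh blood count. The Fecal Samples section opens its own storage sentence by referring back to the same step, which confirms that freezing is the intended handling and not a slip of one word.

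**The case against.** The strongest reply is that a journal article condenses. Tube types, centrifugation, aliquots and the matching of tests to fractions normally sit in the full protocol or a laboratory manual, neither of which is shown. The section never says whole blood, and its panel is evidently shorthand, since total lymphocytes are used elsewhere but not listed. Routine hematology is normally run fresh, and a laboratory asked for a differential on thawed blood would notice at the first sample.

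Much of this is fair. It makes it plausible that the site runs counts fresh and that the article has merged two sample pathways, and it lowers both the severity and the confidence. It does not remove the point. The article does not leave handling unstated: it gives one storage rule for the samples and then a panel that the rule makes partly impossible. The fresh-count reading has to be brought in from outside and runs against the storage sentence.

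Other parts of the reply stand in full. Handling is the same in both arms, so the expected effect is lost information and not a bias between arms. Variables enter the multivariable model only if significant in univariate analysis, and they become mediators only if related to complications, so damage to those analyses is possible but not certain.

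**Conclusion.** Wrong as written; low severity, moderate confidence. If the stated rule is followed, MCV, MCH and the neutrophil-lymphocyte ratio (3 of 12 listed analytes), together with the total lymphocytes used for nutritional status, cannot be measured validly at either visit. The planned analysis of change in the ratio would then have no usable data.

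The conclusion rests on two things: that the storage sentence means what it says for all blood samples, and the elementary fact that frozen and thawed blood has no intact cells to count.

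A reader might go further in three ways that the document does not support.

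- That the whole blood panel is lost. It is not: the seven soluble markers tolerate freezing after separation, hemoglobin can be read in lysed whole blood, and prothrombin time is only at risk.
- That the trial's main result is threatened. The primary endpoint is the complication rate graded at discharge, which uses none of these samples.
- That invalid counts have already been recorded. Nothing in the article shows how any sample was in fact processed.

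**What to change.** Restate the Blood Samples section as two pathways:

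- Full blood count with differential (hemoglobin, MCV, MCH, total lymphocytes, neutrophil-lymphocyte ratio) and prothrombin time: run on fresh anticoagulated blood on the day of collection.
- Batched assays such as IL-6, IL-10 and TNF-α: run on separated serum or plasma aliquots, which alone are frozen. State whether C-reactive protein, albumin, prealbumin and creatinine belong here or with the same-day tests.

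Add total lymphocytes to the listed panel so that it agrees with Nutritional Evaluation.

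The article reports that recruitment began in September 2021, so some patients will already have been sampled. For them, use same-day routine hospital results where they exist, and treat any count obtained from frozen blood as missing.

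The cost is one or two sentences in the sample-handling text. No visit, treatment or clinical decision changes. If counts are already run fresh, practice does not change and only the text is corrected.
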